### Follow‑up schedules

At the 28-day mark, patients will be assessed for the primary outcome of survival or death. At this point, the attending physician will report the primary outcome, and the data collection database will then document the 28-day mortality rate, as well as the duration of ICU and hospital stays, along with other relevant outcomes. During the study period, specific measurements will be taken at predetermined time points: day 1, day 3 ± 1, day 7 ± 1, day 14 ± 2, day 21 ± 2, day 28 ± 2, and before extubation (with priority to day 10 ± 2), discharge or death. The following parameters will be recorded: inflammatory markers, arterial blood gas, coagulation, blood glucose, blood lipids, electrolytes, myocardial enzymes, immune indexes, cell count and classification of BALF and etiological examination. 28-day administration of antibiotics, neuromuscular blockers, vasoactive agent, hormones and immunosuppressants will be tracked. The measurement and collection schedule of this experiment are summarized in the follow-up form (Table 1).

**Table 1 pone.0332985.t001:** The schedule of measurements and visits of this trial.

Timeline (day)	Screening	Follow-up								
	d1	d3 ± 1	d7 ± 1	before extubation (priority: d10 ± 2)	d14 ± 2	d21 ± 2	d28 ± 2	discharged/death (≤28 days)	d1-28	d28
**Informed consent form**	Χ									
**Inclusion/exclusion criteria**	Χ									
**Demographic data**	Χ									
**History of diseases**	Χ									
**ARDS risk factors**	Χ									
**Clinical symptom**	Χ	Χ	Χ	Χ	Χ	Χ	Χ	Χ		
**Imaging**	Χ	Χ	Χ	Χ	Χ	Χ	Χ	Χ		
**APACHE Ⅱ scores**	Χ	Χ	Χ	Χ	Χ	Χ	Χ	Χ		
**SOFA scores**	Χ	Χ	Χ	Χ	Χ	Χ	Χ	Χ		
**mechanical ventilation parameter**	Χ	Χ	Χ	Χ						
**respiratory mechanics**	Χ			Χ						
**pulmonary ultrasound score**	Χ			Χ						
**cardiac echocardiography**	Χ			Χ						
**pulse indicator continuous cardiac output parameters**	Χ			Χ						
**mNGS detection**	Χ									
**Clinical pathogen detection**	Χ	Χ	Χ	Χ	Χ	Χ	Χ	Χ		
**Laboratory examination**	Χ	Χ	Χ	Χ	Χ	Χ	Χ	Χ		
**BALF cell count and classified examination**	Χ			Χ						
**Samples**	Χ			Χ						
**Antibiotic use record**									Χ	
**vasoactive agent use record**									Χ	
**neuromuscular blockers, sedative and analgesic drugs use record**									Χ	
**Adverse events**									Χ	
**28-day survival follow-up**										Χ
**28-day ICU length of stay**										Χ
**28-day ventilator-free days**										Χ

X indicates that the corresponding actions and clinical data will be performed or recorded during the specified time period. Abbreviations: d1: First day of enrollment; ARDS: Acute Respiratory Distress Syndrome; APACHE: Acute Physiology and Chronic Health Evaluation; SOFA: Sequential Organ Failure Assessmentm; mNGS: Metagenomic Next Generation Sequencing; BALF: Bronchoalveolar Lavage Fluid.

### Multi-Omics data analysis and integration

The core objective of day 1 metagenomic testing is to characterize the infection status of patients at the initial stage of intubation, including the presence of infection, pathogenic species, and strain types, thereby providing key references for subsequent patient stratification. Combined metagenomic and viromic analyses focus on unraveling microecological differences at baseline, exploring variations in microbial diversity and background flora composition across distinct patient groups. RNA-seq data aims to capture global differences in early host immune responses, ultimately identifying differentially expressed genes (DEGs) as well as enriched metabolic pathways and gene ontologies (GO terms). Single-cell transcriptomics enables more refined dissection of immune response patterns, clarifying heterogeneous differences in immune regulation among individual patients. Proteomics and metabolomics, respectively, investigate metabolism-specific and protein-specific differential molecules involved in the host immune processes of patients with divergent outcomes (survival vs. death), comprehensively covering functional molecular variations linked to immune regulation. While single-omics analyses can initially yield a large set of differential markers, subsequent multi-omics integration is essential to further prioritize and narrow down core candidate markers.

To accurately identify key regulatory factors, cross-omics integrated screening of proteomic, metabolomic, transcriptomic, and microecological data will first be performed, using gene function or metabolic pathways as core dimensions to extract overlapping or strongly correlated modules of differential molecules across omics. This process will eliminate functionally irrelevant redundant information, ultimately selecting core differential markers that are co-occurring across multiple omics and closely associated with prognostic phenotypes (e.g., survival/death). Data preprocessing will be required prior to model construction: the screened core marker data will be integrated, Z-score standardization will be applied to eliminate dimensional discrepancies across different omics platforms, and the dataset will be randomly partitioned into a training set (for model development) and a test set (for preliminary validation) at a ratio of 8:2 to mitigate overfitting risks at the data level. In this process, samples from eight centers will be selected as training dataset according to the final number of enrolled patients, while the other two centers will act as validation set. The feature dimensionality reduction stage will employ a combined “unsupervised + supervised” strategy: unsupervised dimensionality reduction will first be conducted via principal component analysis (PCA), retaining principal components with a cumulative variance contribution rate > 80% to initially compress feature dimensions; subsequently, least absolute shrinkage and selection oerator (LASSO) will be applied for supervised dimensionality reduction, selecting features with non-zero coefficients to exclude irrelevant variables. For advanced applications, principal component regression (PCR) or partial least squares discriminant analysis (PLS-DA) will be integrated to further prioritize core features strongly correlated with prognostic phenotypes, ultimately refining high-dimensional features to 20–50 variables to balance model complexity and predictive performance. For model construction, appropriate multi-omics fusion strategies will be selected. For early fusion, all core omics features will be integrated first, followed by building a unified predictive model using algorithms such as random forest (RF) or support vector machine (SVM). For late fusion, individual predictive models will be constructed for each omics separately, and the results will then be integrated via weighted voting (e.g., transcriptomics model weight = 0.4, metabolomics = 0.3, proteomics = 0.3) or the Stacking ensemble method to improve prediction stability. Common tools to be utilized include the multi-omics prediction module in MetaboAnalyst and ensemble learning libraries within Python’s scikit-learn. Model performance will be rigorously evaluated using standardized metrics: classification models (e.g., survival/death prognostic prediction) will be quantified using accuracy, sensitivity, specificity, area under the ROC curve (AUC), and confusion matrix. Regression models (e.g., prognostic risk score prediction) will assess fitting efficacy using coefficient of determination (R²), root mean square error (RMSE), and mean absolute error (MAE). Notably, AUC ≥ 0.85 (for classification models) and R² ≥ 0.7 (for regression models) will be established as key criteria for confirming the clinical utility of the model.

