### Participant recruitment

Participants will be recruited from ten medical centers in tertiary general hospitals in North China, including the First Medical Center of Chinese PLA General Hospital, the Sixth Medical Center of Chinese PLA General Hospital, the Eighth Medical Center of Chinese PLA General Hospital, Beijing Shijitan Hospital, Beijing Anzhen Hospital, AMHT Group Aerospace 731 Hospital, Zhengzhou Central Hospital, Henan Provincial People’s Hospital, the First Affiliated Hospital of Zhengzhou University and First Hospital of Shanxi Medical University.

Patients with ARDS will be invited to participate in this study upon admitting the branch center. Those who meet the inclusion criteria and provide signed informed consent will enter the screening period (S1 File). During the screening visit, trained researchers (physicians) will confirm the eligibility based on symptoms, laboratory results, and chest X-ray or CT image, and review every inclusion and exclusion criterias. Patients who meet the exclusion criteria will be excluded from this study within 24 hours. The recruitment period is set for 24 months, spanning from November 2023 to November 2025.

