### Inclusion and exclusion criteria

In this study protocol, patients with moderate or severe ARDS and experienced mechanical ventilation will be included for inclusion selection. The definition of ARDS refers to the Berlin definition of ARDS [3]. The core diagnostic criteria include: an onset time within 1 week after a known clinical insult or the onset of new/worsening respiratory symptoms; chest imaging findings of bilateral lung opacity or patchy shadows that cannot be fully explained by conditions such as pleural effusion, atelectasis, or nodules; respiratory failure that cannot be fully attributed to heart failure or fluid overload, with objective examinations such as echocardiography required to rule out hydrostatic pulmonary edema in the absence of clear predisposing risk factors; and disease severity classified into three grades based on the oxygenation index (PaO₂/FiO₂) combined with a positive end-expiratory pressure (PEEP ≥ 5 cmH₂O): mild (200 mmHg < PaO₂/FiO₂ ≤ 300 mmHg, with continuous positive airway pressure ventilation permitted), moderate (100 mmHg < PaO₂/FiO₂ ≤ 200 mmHg), and severe (PaO₂/FiO₂ ≤ 100 mmHg). Patients with moderate or severe ARDS will be included.

Patients meeting any of the following criteria will be excluded from the study:

Patients aged less than 18 years old.Patients with intracranial hypertension, acute coronary syndrome, pleural fistula, pneumothorax, and subcutaneous emphysema.Pregnant and lactating patients.Patients with severe hemodynamic instability (vasopressor dose increased by >30% within the first 6 hours, or noradrenaline dose > 0.5 μg/kg/min).Patients who do not agree to participate in this study and patients do not sign the informed consent.

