### Sample collection, and multi-omics profiling

For enrolled patients, peripheral blood and BALF samples will be collected at two time points: within 24h after enrollment and before tracheal extubation. For patients who cannot be extubated within 7–14 days, samples will be collected during this 7–14 day window, with priority given to day 10 ± 2 (Fig 2).

For blood sampling, patients must be in a fasting state prior to blood collection. A total of 10–15 mL of blood will be collected using anticoagulant tubes, which will then undergo pretreatment before separate storage or detection. Within four hours of sampling, centrifugation will be conducted at 3000 r/min for 10 minutes. The resulting plasma will be aliquoted into 1.5 mL EP tubes at 500 μL per tube for subsequent proteomics and metabolites detection. For the remaining sample, equal volumes of phosphate buffered saline (PBS) and Ficoll lymphocyte separation solution will be added, followed by centrifugation at 1000g for 20 minutes to collect PBMCs. After adding 5 mL of PBS, the mixture will be centrifuged at 400g for 5 minutes, the supernatant will be discarded, and PBMCs will be resuspended in cell cryopreservation solution before aliquoting into EP tubes at 1 mL per tube. The PBMC samples will be used for RNA-seq and scRNA-seq. The samples will be stored at −80°C before multi-omics detection.

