## Discussion

ARDS remains a critical challenge in critical care medicine, primarily due to its striking heterogeneity across etiology, pathophysiology, clinical presentation, and imaging characteristics, which has hindered the development of universally effective therapies [4,5,29]. While recent advancements in medical and biological technologies have deepened our understanding of this heterogeneity, significant gaps persist in translating such insights into improved patient outcomes [30]. Against this backdrop, the paradigm of precision medicine has emerged as a transformative approach, emphasizing the need to tailor diagnosis and treatment to individual patient characteristics [31,32]. This shift has underscored the core value of integrating advanced technologies such as molecular biology, bioinformatics, scRNA-seq, RNA-seq, microbiome analysis, proteomics, and metabolomics into ARDS research. These technical approaches hold promise for unraveling dynamic change patterns of key molecules, signaling pathways, and cell subsets during ARDS initiation and progression, ultimately enabling individualized and targeted therapeutic strategies. Such efforts not only represent the future direction of ARDS research but also strive to break through the limitations of the current “one-size-fits-all” treatment model.

The present study protocol contributes to this evolving landscape through several key strengths. It is the first large-scale, multicenter observational cohort study with rigorous quality control, focused on mechanically ventilated patients with moderate to severe ARDS. By systematically collecting comprehensive baseline and clinical data, alongside BALF and peripheral blood samples at two critical time points (day 1 post-admission and pre-extubation), the study protocol enables in-depth multi-omics analyses.

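### Day 1 is the enrolment day, yet its samples are read as showing the start of intubation and the early host response, and no entry rule limits ventilation before enrolment

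*Protocol article*

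**What the plan says.** **Timing of the sample.** The section on sample collection takes blood and lavage fluid "within 24h after enrollment and before tracheal extubation". The footnote to Table 1 gives "d1: First day of enrollment", and the table numbers its visits up to day 28 on that same scale.

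**Entry.** Under Inclusion and exclusion criteria, "patients with moderate or severe ARDS and experienced mechanical ventilation will be included for inclusion selection". The only time window in the disease definition is the Berlin one: "an onset time within 1 week after a known clinical insult or the onset of new/worsening respiratory symptoms". Participant recruitment adds: "Patients with ARDS will be invited to participate in this study upon admitting the branch center".

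**Interpretation.** The section on multi-omics analysis states: "The core objective of day 1 metagenomic testing is to characterize the infection status of patients at the initial stage of intubation". It uses that infection status as a key input to patient stratification and assigns bulk RNA sequencing to differences in the early immune response. The Discussion describes the two sampling times as "day 1 post-admission and pre-extubation".

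**The concern.** Enrolment, intubation and admission are three different events. A sample taken on the enrolment day describes the start of intubation only if enrolment follows intubation closely, and the printed entry rules do not ensure that. As written, a patient intubated a few hours ago and a patient transferred after two weeks of ventilation could both be enrolled, and both would give a day-1 sample.

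This touches the core analysis. Day-1 flora, pathogens, host transcriptome and respiratory mechanics are to be compared between survivors and non-survivors and then screened as model features. Time already spent on the ventilator, with the antibiotic exposure and hospital-acquired organisms that can come with it, may change all of these, and it may also be related to 28-day death. If so, a marker of ventilation duration could be reported as a marker of early ARDS biology. The protocol also plans to train on eight centres and validate on two. If prior ventilation time differs between centres, the difference could carry into the validation. The document contains nothing that shows whether it does.

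**Working it through.** No stated figure is in dispute, so the check is mainly a comparison of texts.

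**Step 1: the operational origin.** The sampling section, the abstract, both figure legends and the Table 1 footnote tie the first sample to enrolment; the Outcomes section ties it to inclusion. The Follow-up section does not name an origin for the 28-day mark, but Table 1 counts its days from d1. Sample and outcome clock therefore share one origin within each patient: enrolment.

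**Step 2: what the interpretation requires.** Reading the sample as intubation-stage requires time from intubation to enrolment to be short. Reading it as post-admission requires time from admission to enrolment to be short.

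**Step 3: whether any entry rule ensures the first of these.**
- The ventilation criterion, "patients with moderate or severe ARDS and experienced mechanical ventilation will be included for inclusion selection", gives no maximum duration.
- The Berlin one-week clause runs from insult or symptoms to ARDS onset. It does not limit onset to enrolment or intubation to enrolment.
- Invitation on admission to the centre does not limit ventilation given elsewhere before transfer, or a later enrolment.
- The 24-hour statement in Participant recruitment concerns removal of patients who meet an exclusion criterion.
- The exclusion list covers age, named acute conditions, pregnancy and lactation, haemodynamic instability, and absence of consent. None of these limits ventilation time.

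No rule in the printed text supplies the limit.

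**Step 4: illustration of whether baseline risk could differ.** Inputs: 28-day mortality of 40% (Sample size calculation). Assumptions: the 40% is counted from intubation, which the document does not say, and the hazard is Weibull with shape k, for which the document gives no value.

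Cumulative hazard from intubation: H(t) = −ln(0.6) × (t/28)^k. Mortality over 28 days for a patient enrolled on ventilation day t: 1 − exp{−[H(28+t) − H(t)]}.

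| Shape k | t = 0 | t = 3 | t = 7 | t = 14 |
|---|---|---|---|---|
| 0.6 (hazard falling) | 40% | 34% | 30% | 27% |
| 0.8 | 40% | 37% | 36% | 34% |
| 1.0 (constant) | 40% | 40% | 40% | 40% |
| 1.3 (hazard rising) | 40% | 43% | 45% | 48% |

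Worked cell, k = 0.6 and t = 14: −ln(0.6) = 0.511; 1.5^0.6 − 0.5^0.6 = 1.275 − 0.660 = 0.616; 0.511 × 0.616 = 0.314; 1 − exp(−0.314) = 27%.

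Whether prior ventilation time shifts 28-day risk, and in which direction, depends on a hazard shape that is not known. Its possible effect on the day-1 biology does not depend on that shape.

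**The case against.** The strongest reply is that day 1 has a single working definition. Every passage that a site would follow times it from enrolment or inclusion; the intubation and admission phrases are an analytic aim and Discussion prose. Prediction among patients alive and ventilated at enrolment is also a legitimate target, and prior ventilation time is then ordinary case mix. This stands, and it narrows the point to interpretation and confounding.

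It also rules out several stronger readings that a reader might infer:

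- *The sample and the 28-day clock start at different times in the same patient.* They do not; both run from enrolment. Only the stage of illness at that origin can differ, and it differs between patients.
- *Ventilation need not be invasive or ongoing.* The entry phrase is loose, but the Fig 1 legend and Outcomes both speak of invasive ventilation, and the second sample presupposes a tube in place.
- *The intubation date is not recorded.* The data-collection list does not name it, but the case report forms in the supplementary files are not shown and may hold it.
- *Deaths before entry show a distorted outcome.* Under a constant hazard giving 40% at 28 days, 1 − exp(ln(0.6) × t/28) gives 5.3%, 12.0% and 22.5% dead by days 3, 7 and 14. These are deaths before entry. Under the same assumption, 28-day mortality from enrolment stays at 40%.

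What the reply does not answer is that the early-stage label is printed, feeds patient stratification and the survivor comparison, and is not secured by the eligibility text. The criteria are printed with their exclusions, so this is not just detail that an article leaves to a longer document.

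**Conclusion.** The point holds as a mismatch between how day 1 is defined and how it is interpreted. Enrolment is the origin, the interpretation assumes closeness to intubation, and nothing in the entry rules secures that closeness. Patients at different ventilation stages can be pooled in the day-1 survivor-versus-death comparisons, with prior ventilation time as a possible confounder.

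The size cannot be stated, because neither the share of late enrolees nor the distribution of ventilation time before enrolment is given. If nearly all patients are enrolled soon after intubation, the effect is small and only the wording needs repair. The 27% to 48% range at a 14-day delay is an illustration under assumed hazard shapes and is not an estimate for this cohort. The mismatch in the text is certain; the confounding is plausible but unmeasured. The change is worth making because it is cheap and protects the main biological claim.

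**What to change.** - State once that day 1 is the first day of enrolment, and bring the Multi-Omics section and the Discussion into line with the Table 1 footnote.
- Confirm that the case report form holds the date of intubation and the date on which the moderate or severe ARDS criteria were first met. If not, take both from the chart.
- Report the distribution of ventilation days before enrolment, overall and by centre.
- Include ventilation days before enrolment as a covariate in the day-1 survivor-versus-death comparisons and offer it to the model as a candidate clinical predictor.
- Repeat the main analysis in early enrolees, with the limit that defines them fixed before outcomes are examined. Keep the intubation-stage and early-response wording for that subset.

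A new entry limit is not proposed: recruitment began in November 2023 and was due to end in November 2025, so it would reach few patients and split eligibility within the cohort.

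Cost: one more covariate, one sensitivity analysis in a smaller and so less precise subset, a wording change and, if the dates are not already recorded, two chart dates per patient.

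### Markers are screened against survival/death before the train/test split, so the test-set AUC is biased upward and can exceed 0.85 on pure noise

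*Protocol article*

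**What the plan says.** All of this is in the protocol article, Multi-Omics data analysis and integration, unless stated otherwise.

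- **Single-omics step.** Proteomics and metabolomics look for "differential molecules involved in the host immune processes of patients with divergent outcomes (survival vs. death". Outcome is therefore already the grouping variable here.
- **Cross-omics step.** "cross-omics integrated screening of proteomic, metabolomic, transcriptomic, and microecological data will first be performed", "ultimately selecting core differential markers that are co-occurring across multiple omics and closely associated with prognostic phenotypes (e.g., survival/death".
- **Preprocessing.** After that, "the screened core marker data will be integrated, Z-score standardization will be applied".
- **Split.** Next in the same sentence, "the dataset will be randomly partitioned into a training set (for model development) and a test set (for preliminary validation) at a ratio of 8:2". The stated purpose is to limit overfitting.
- **Centre-based split.** The following sentence adds that "samples from eight centers will be selected as training dataset according to the final number of enrolled patients", with the other two centres used for validation.
- **Modelling.** PCA, LASSO, optional PCR or PLS-DA, and random forest or SVM are described after the split. They end with 20 to 50 variables.
- **Criterion.** An AUC of at least 0.85 is a key criterion for the model's clinical utility. The Sample size calculation section sets an AUC of 0.85 against 0.70.

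**The concern.** A held-out set gives an unbiased AUC only if its outcomes played no part in building the model. Here the data being split have already been reduced to markers that separate survivors from non-survivors. A noise marker that passes the screen does so because the groups happen to differ on it in these particular patients, including those later called test patients. The difference is therefore still there when the model is tested.

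The split can still expose overfitting from the steps that follow it (PCA, LASSO, classifier fitting). It cannot expose overfitting from the outcome-based screen, which is the step that searches the largest number of variables.

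At stake is the claim attached to the AUC. If an uninformative marker set can pass 0.85, passing does not show prognostic value.

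**Working it through.** **1. The plan's own figure.** Inputs (Sample size calculation): AUC 0.85 against 0.70, α = 0.05, β = 0.10, loss under 10%, mortality 40%. The variance formula, two-sided testing and a 1:1 ratio are assumptions, chosen because they reproduce the stated figure.

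The binormal variance per death is V = 0.0099·exp(−a²/2)·[(5a² + 8) + (a² + 8)/R], with a = 1.414·Φ⁻¹(AUC) and R = 1.

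- AUC 0.70: a² = 0.55, V₀ = 0.145, √V₀ = 0.381.
- AUC 0.85: a² = 2.148, V₁ = 0.0977, √V₁ = 0.313.
- Deaths = [(1.96 × 0.381 + 1.282 × 0.313)/0.15]² ≈ 58.5, so 59.
- 59/0.9 = 65.6, so 66. Then 66/0.40 = 165.

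The 66 deaths and 165 patients reproduce. The calculation presumes an unbiased AUC.

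**2. Size of the test set.** 20% of 165 is 33 patients, about 13 deaths (0.2 × 66 = 13.2) and 20 survivors (0.2 × 99 = 19.8). At a true AUC of 0.50 the standard error is about 0.10, so 0.85 lies (0.85 − 0.50)/0.10 = 3.5 standard errors away. Without leakage, a useless model should almost never reach 0.85.

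**3. Hand check of the leak.** Take 500 independent noise markers and screen all 165 patients at |t| > 1.97 (about 5% two-sided).

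- By chance 0.05 × 500 = 25 markers pass.
- A marker just at the threshold has a standardised difference d = 1.97 × √(1/66 + 1/99) = 1.97 × 0.159 = 0.313 in the whole cohort. A random test subset has the same expected difference.
- With k independent markers, equally weighted and correctly signed, AUC = Φ(d·√(k/2)) = Φ(0.313 × √12.5) = Φ(1.107) ≈ 0.87.

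So 25 noise markers at the threshold are enough to put the expected test AUC at about 0.87.

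**4. Simulation on pure noise.** 40% deaths, 8:2 split, markers screened by t-statistic on survival/death before the split. The fitted chains were a diagonal linear classifier, training-set PCA plus ridge, and training-set PCA plus LASSO followed by SVM or random forest.

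| Setting | Candidates | Mean test AUC | Runs ≥ 0.85 |
|---|---|---|---|
| Linear classifier, N = 165, top 20–50 | 500 | 0.84–0.90 | 49–81% |
| same | 2,000 | 0.90–0.96 | 84–100% |
| same | 20,000 | 0.95–0.99 | 99–100% |
| PCA + ridge, N = 165 | 200 | 0.78–0.79 | 19–28% |
| same | 1,000 | 0.87–0.93 | 68–96% |
| same | 5,000 | 0.92–0.98 | 95–100% |
| PCA + ridge, N = 200 | 200 | 0.76–0.77 | 10–13% |
| same | 1,000 | 0.85–0.91 | 47–92% |
| same | 5,000 | 0.90–0.97 | 90–100% |
| PCA + LASSO, SVM or RF, N = 165 or 200 | 5,000 | 0.95–0.975 | 100% |
| same, N = 200, blocks of 50 with ρ = 0.5 | 1,000 | 0.72–0.78 | 3–15% |
| same, blocks | 5,000 | 0.84–0.94 | 40–100% |
| same, blocks | 20,000 | 0.97–0.985 | 100% |

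A further PCA-plus-ridge run at N = 165 and 200 gave 0.60–0.92 with 200–1,000 candidates and about 0.84–0.99 with 5,000–20,000, with features independent or in correlated blocks.

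**5. Cross-omics overlap.** The plan keeps markers that co-occur across omics. This was imitated with N = 165, three omics layers and 300 pathways, keeping a differential marker only if its pathway was hit in at least two layers.

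- 14,100 candidates: 0.87–1.00, with 67–100% of runs at or above 0.85.
- 2,300 candidates, |t| > 1.97: 0.83–0.85, with 44–51%.
- 2,300 candidates, |t| > 2.6: often fewer than three markers remained; where a model could be fitted, 0.67–0.74, with 0–18%.

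Holding out two of ten centres instead of a random 20% gave similar results.

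**6. The same chains with screening in training patients only.** Mean test AUC was 0.47–0.53. Where the share of runs at or above 0.85 was recorded, it was 0% in every setting.

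**The case against.** - **The text never says the whole cohort is screened.** True; it is inferred from the order, and a condensed article is weaker evidence of order than an analysis plan. The training centres depend on enrolment numbers and could be named before any screening. But the article puts screening first, splits data it describes as already screened, and nowhere limits screening to training patients. Followed as written, it leaks.
- **The eight-versus-two-centre split may be the real validation.** It is also described after screening, so it does not cure the problem.
- **Pooled Z-scoring does little harm.** Correct. It ignores outcome, and the finding does not depend on it.
- **The AUC test is not explicitly tied to held-out patients, and the study calls itself exploratory.** The Sample size calculation section does not name the test set, the Statistical analysis section describes a Cox model with no split, and the Discussion asks for independent validation. This softens the consequence but does not remove it, because the section with the split also attaches clinical utility to an AUC of 0.85.
- **The size depends on assumptions.** This stands. Candidate numbers, correlation and threshold are not given. The 20 to 50 variables in the plan are the final count, not the number kept by the screen. With few or strongly correlated candidates only some noise runs reach 0.85.

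**Conclusion.** The concern holds and must be fixed. As ordered in the text, the outcome-based screen uses the patients who later serve as the test set, so the test AUC is biased upward. This is a workflow stated wrongly, not detail left to another document.

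The true AUC in these simulations is 0.50. Without the overlap step, the mean reported AUC was 0.60 to 0.93 for 200 to 1,000 candidates and 0.84 to 0.99 for 5,000 to 20,000; with the larger numbers 40% to 100% of noise runs met the 0.85 criterion. The overlap requirement changes the size, and a strict threshold with few candidates shrinks it considerably. That the planned platforms will yield thousands of candidates is an assumption, though a natural one for bulk RNA sequencing with proteomics and metabolomics. That the AUC can exceed 0.85 on noise does not depend on the upper end of that range. The R² ≥ 0.7 criterion for regression models is open to the same leak; it was not simulated.

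**What to change.** Reverse the order in Multi-Omics data analysis and integration:

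1. State which held-out set counts, the random 20% or the two centres, and fix its members before any omics comparison by outcome.
2. In training patients only, or within each training fold if resampling is used, carry out the survivor/non-survivor comparisons, cross-omics overlap screening, Z-score means and SDs, PCA, LASSO, any PCR or PLS-DA, tuning and fusion weights.
3. Freeze the whole chain and apply it once to the held-out patients. Judge the 0.85 criterion on that AUC, with its confidence interval.
4. Whole-cohort differential analyses may be reported as descriptive, but must not feed the validated model.

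The cost is a re-ordered pipeline and some computing time, with no new patients, samples or assays. The sample-handling section sends samples for multi-omics analysis only after all patients are enrolled, so the held-out set can be fixed beforehand. The reported AUC will probably be lower, but it will be interpretable.
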